### Secondary outcomes

3.2

The protocol may provide subsidies for the implementation of new aerobic physical exercise programs for patients with CRD, to help improve their well-being and QoL.

### Data analysis

3.3

The data will be analyzed using the Statistical Package for Social Science (SPSS), version 22.0. Descriptive analysis will be performed for all variables. Data will be expressed as mean ± standard deviation or median (interquartile range), where appropriate. The distribution of the sample will be tested with the Shapiro–Wilk test. For the comparison of the initial and final values between groups, the unpaired Student *t* test for parametric distributions and the Mann–Whitney test for nonparametric distributions will be applied. Statistical significance will be considered at the *P* < .05 (or 5%) level.

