## Methods

2

This study protocol will follow the items of the Standard Protocol for Randomized Trials (SPIRIT). This is an open, single-group experimental study on the autonomic heart rate modulation response under the effects of aerobic training during hemodialysis sessions in patients with CRD.

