### Instruments and data collection

2.6

The HRV assessment instrument will be applied at the beginning and end of the aerobic exercise protocol. Initially, the sample size will be 40 adult patients with CRD who undergo hemodialysis in a study with a single screening group. The present study aims to evaluate the effects of supervised aerobic exercise in cycloergometry performed in patients with CRD during hemodialysis sessions, using HRV analysis.

The kidney disease quality of life short form (KDQOL-SF)^[20]^ will specifically evaluate the QoL of the patients with CRD at the Hospital das Clínicas do Rio Branco-Acre. The international physical activity questionnaire (IPAQ) will be used to identify the level of physical activity that the patients are currently experiencing.^[21]^ In addition, information will be collected regarding the laboratory parameters of the patient's charts, and these data will be collected from the month referring to the application of the experimental protocol (Fig. 1).

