**Figure 2 F2:**
[figure not shown]
Placement of the strap on the patient. Source: Prepared by the authors, 2018.^[23]^

The recorded pulses will be directed to a computer through an infrared signal emitting interface for the analysis of the ventricular function curve (VFC) by the Polar Precision Performance software. For data analysis, the VFC will be filtered at a moderate intensity for the elimination of ectopic beats and/or noises. The HRV analysis will be performed in time and frequency domain and nonlinear methods (Fig. 3).

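### A Shapiro–Wilk test picks between two unpaired tests in a single-group before/after study, so the quantity tested is set by the data and the within-patient change is never analysed

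*Protocol article*

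**What the plan says.** Section 3.3 of the protocol article sets a two-stage rule. First, "The distribution of the sample will be tested with the Shapiro–Wilk test". Then: "For the comparison of the initial and final values between groups, the unpaired Student *t* test for parametric distributions", while "the Mann–Whitney test for nonparametric distributions will be applied" otherwise. The threshold is given as "Statistical significance will be considered at the *P* < .05 (or 5%) level"; sidedness and the pre-test's own cut-off are not stated.

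The design is described elsewhere. Methods (section 2): "This is an open, single-group experimental study". Instruments and data collection (2.6): "Initially, the sample size will be 40 adult patients with CRD who undergo hemodialysis in a study with a single screening group", with HRV recorded at the start and end of the programme. Section 2.7 says the same evaluation is repeated after 3 months. Several indices will pass through the rule, since "The HRV analysis will be performed in time and frequency domain and nonlinear methods".

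The article gives no SD, skewness, start-to-end correlation, effect size or power, and mentions neither a paired test nor a transformation.

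**The concern.** There are two linked problems in what the section fixes.

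1. **The quantity tested is left to the data.** The t test addresses a difference in means; Mann–Whitney addresses a rank shift. Applied to each index in turn, the rule can send one index to the first and another to the second, so results need not be comparable across indices. The input is also undefined: the text does not say whether the sample's distribution means the raw values at each visit or the within-patient changes, and the two can give different answers.

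2. **Both branches are unpaired.** Whichever test is chosen, the initial and final values of the same patients are treated as coming from different people. The within-patient change is not analysed by either route.

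The stake is a 40-patient study that may fail to detect a real change, and that reports effects on a footing not settled in advance.

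**Working it through.** **No figure to reproduce.** The article states n = 40 without effect size, SD or power. Every input below other than n = 40 and the 5% level is an assumption; tests are taken as two-sided and the pre-test cut-off as 0.05.

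**Step 1: what unpaired testing does to paired data.** Let ρ be the correlation between initial and final values and δ the shift in SD units. The unpaired test uses a standard error of SD·√(2/n); the true one is SD·√(2(1−ρ)/n). With n = 40, in the normal approximation:

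- Actual type I error = 2[1 − Φ(1.96/√(1−ρ))]. At ρ = 0.5: 1.96/0.707 = 2.77, giving 0.006. Simulation of the full rule gave 0.006–0.009.
- Power of the unpaired test = Φ((δ/√(2/40) − 1.96)/√(1−ρ)). At δ = 0.4, ρ = 0.5: (1.789 − 1.960)/0.707 = −0.24, giving 0.40.
- Power of the paired test = Φ(δ√40/√(2(1−ρ)) − 1.96). At the same values: 2.530 − 1.960 = 0.570, giving 0.72 (0.69 by the noncentral t).

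**Step 2: does the test switch?** Simulated n = 40, Shapiro–Wilk on both raw samples. The t test is chosen in about 90% of runs for a normal index, 42% at log SD 0.25, 2% at 0.5 and 0% at 0.8 or above. The choice also depends on what is examined. For log-normal indices (log SD 0.4–1.0, ρ 0.4–0.8), normality is rejected in 85–100% of runs on raw values and 29–95% on differences. The two readings pick different tests in 57–64% of runs at log SD 0.4, 24–31% at 0.7 and 6–7% at 1.0.

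**Step 3: where the power goes.** Log-normal index, n = 40, ρ = 0.5, δ = 0.4 log-scale SD:

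| Analysis | log SD 0.5 | log SD 0.8 | log SD 1.0 |
|---|---|---|---|
| Rule as written (unpaired) | 0.369 | 0.369 | 0.374 |
| Same pre-test on raw values, paired t or signed-rank | 0.658 | 0.604 | 0.599 |
| Signed-rank, no pre-test | 0.658 | 0.604 | 0.599 |
| Fixed paired t on logs | 0.696 | 0.690 | 0.680 |

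At log SD 0.8, pairing adds 0.604 − 0.369 = 23.5 points, removing the pre-test in favour of signed-rank adds 0, and the log scale adds 0.690 − 0.604 = 8.6 points. At ρ = 0 the rule as written and the paired log test are about equal (0.40–0.41 v 0.41–0.42); the gap is about 15 points at ρ = 0.3 and 52–54 at ρ = 0.7.

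**Step 4: a second set of assumptions.** With a true change of 0.45 SD of the log differences, log SD 0.4–1.0 and ρ 0.4–0.8, the rule as written has 8–58% power and the fixed paired log test 78–81%. The pre-test with paired tests falls 4–11 points below the log test. At log SD 1.0, ρ = 0.8, the paired pre-test rule has 0.70, signed-rank 0.70 and raw paired t 0.51.

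**Step 5: is the log scale always better?** No. For a normal index with CV 0.3–0.4 (ρ = 0.6), the paired pre-test rule has 0.79–0.80 and the log t test 0.68–0.74. For skewed patient levels with an additive change, the paired pre-test rule has 0.77–0.80 and the log t test 0.72 (log SD 0.7) or 0.65 (log SD 1.0).

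**The case against.** The strongest reply is that the pre-test does little harm. With paired tests it performs as well as the better raw-scale test and protects against the worse one, and deleting it alone would recover no power. This stands. A reader might infer that the Shapiro–Wilk step is what costs the power; step 3 shows that the unpaired tests do.

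A reader might also convert the log-scale gain into patients. Going from 77% or 71% power to 80% corresponds to (1.96 + 0.84)²/(1.96 + 0.74)² = 1.08 or (1.96 + 0.84)²/(1.96 + 0.55)² = 1.24, so 8–24% more patients. That holds only under log-normality with proportional change, the model for which a t test on logs is ideal. The article gives no distribution for any index, and under other plausible inputs the sign reverses. A mandatory log scale is therefore not supported.

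It can further be said that a condensed article commonly leaves scale and confidence intervals to a fuller plan. That is fair, and their absence is not the point here. The point is the rule that the article does state, which names unpaired tests for one group measured twice and lets the data choose between them.

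Finally, nobody should read this as a false-positive problem. The paired versions stay near 5%, and the rule as written is conservative when ρ is positive.

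**Conclusion.** The concern holds in limited form. Section 3.3 fixes a data-driven choice between two unpaired tests where a single pre-specified analysis of within-patient change is needed. That the tested quantity can shift between indices, and that the target of the pre-test is undefined, follow from the text and need no assumed numbers.

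The size of the power loss does rest on assumptions. At δ = 0.4 SD it runs from about nil at ρ = 0 to 52–54 points at ρ = 0.7, nearly all of it due to ignoring the pairing. The pre-test itself costs almost nothing on the raw scale once tests are paired. The choice of scale is worth about 4–11 points in favour of logs for log-normal indices with proportional change, and works against logs for normal or additive-change indices.

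**What to change.** In section 3.3:

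- Delete the Shapiro–Wilk selection rule and both unpaired tests.
- For each HRV index and each KDQOL-SF score, pre-specify one paired analysis of within-patient change (final minus initial), reported with its effect estimate and 95% CI.
- Fix the scale of each index in advance: natural log with a geometric mean ratio where the index is positive and its change is expected to be proportional; otherwise the index's own scale.
- Give the Wilcoxon signed-rank test as a sensitivity analysis.

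The cost is a few sentences and no new data. The downsides are that log-scaled indices are reported as ratios and need a stated handling of any zeros, and that some power is lost if the scale chosen in advance turns out to be wrong.

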### Intervention

2.5

Liao et al^[17]^ used 2 groups of 20 patients each, performing a 30-minute exercise program consisting of a 5-minute warm-up, 20-minute electric bicycle, and a 5-minute cooling down regimen during treatment with hemodialysis in the renal unit. The exercise was performed under the supervision of a physician and a rehabilitation nurse. This was adapted in this study to be conducted in a single screening group. We also modified the procedure since the exercise will be performed on a mechanical cycle ergometer, facilitating the individualized development for each patient. The work will be overseen by a leading researcher/professional physical educator, following specific medical assessment of the site's nephrology sector.

Marques et al^[18]^ used the Borg perceived effort scale in his program to measure exercise intensity. In our case, the patients will perform aerobic exercise consisting of cyclic movements of the lower limbs. The load will be prescribed by taking into account the Karvonen scale. In Raimundo et al,^[19]^ the subjects were walked on a treadmill for aerobic exercises divided into 5 minutes of warm-up and 25 minutes of exercise, reaching 50% to 70% of their maximal HR (HR_max_). This protocol was modified so that the patients perform the aerobic exercise of cyclical movements of the lower limbs with 45% to 60% intensity of their HR_max_. The total time will be 30 minutes. They will be instructed to remain with arms extended normally in the extension of the chair next to the body, to be accommodated in the best possible way during hemodialysis. The lower limbs will perform the most active part of the exercise by executing a constant rotation of the pedals throughout the aerobic exercise in the mechanical cycler. Patients will be encouraged to increase their intensity according to individual capacity, respecting the principle of biologic individuality. Thus, our protocol consists of developing aerobic exercise 3 times a week, lasting 30 minutes for 3 months, with aerobic intensity, varying from 45% to 60% HR_max_, totaling 36 sessions.

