### Protocol's Phase Study

2.7

This protocol will be done in 3 phases:

T1: Resting stage (duration of 10 minutes): At this stage, the patient will be instructed to remain as relaxed as possible on the stretcher. They will be instructed to remain with arms extended normally in the extension of the chair next to the body, accommodated in the best possible way.T2: Intervention stage (duration of 30 minutes): Patients will perform aerobic exercise consisting of cyclic movements of the lower limbs with 45% to 60% intensity of their HR_max_. They will be instructed to remain with arms extended normally in the extension of the chair next to the body, accommodated in the best way possible (Fig. 4).The lower limbs will perform a constant rotation (pedaling) throughout the aerobic exercise in the lower leg cycle ergometer. (Mini Bike Compact - E 14) from ACTE, with multifunction LCD: scan, time, ODO-RPM, distance, calories, speed, measuring (A × C × L) 49 × 41.5 × 34.5 m, to perform aerobic exercise (Fig. 5).The patients will start pedaling and will be encouraged to increase the intensity so that it reaches the established zone, and will possibly be able to exceed the upper limit, until the intervention time is over. The load was prescribed by taking into account the Karvonen scale.T3: Recovery phase (duration of 20 minutes): Patients will be advised to be as relaxed as possible in the resting phase (recovery). All the patients will be evaluated with the instrument in the initial phase of the research to collect the HRV before the protocol of aerobic exercises proposed during one hour of hemodialysis session (as it appears in the exercise program proposed above). This same evaluation will be carried out with the same characteristics after 3 months.

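### The only tests named are for two independent groups, but the trial measures one group twice; with positive within-patient correlation, standard errors are too large and much power is lost.

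*Protocol article*

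**What the plan says.** The design is stated consistently as a single group measured twice.

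- Section 2 (Methods): "This is an open, single-group experimental study on the autonomic heart rate modulation response".
- Section 2.5 (Intervention), after describing a cited study with two groups of 20: "This was adapted in this study to be conducted in a single screening group".
- Section 2.6 (Instruments and data collection): "Initially, the sample size will be 40 adult patients with CRD who undergo hemodialysis in a study with a single screening group". On timing: "The HRV assessment instrument will be applied at the beginning and end of the aerobic exercise protocol".
- Section 2.7 (Protocol's Phase Study), on the initial HRV evaluation of all patients: "This same evaluation will be carried out with the same characteristics after 3 months".

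Section 3.3 (Data analysis) is the only place where inference is described. On normality: "The distribution of the sample will be tested with the Shapiro–Wilk test". Then: "For the comparison of the initial and final values between groups, the unpaired Student" *t* test is to be used for parametric distributions and the Mann–Whitney test otherwise, at the 5% level. Neither a paired test nor a repeated-measures model is mentioned in the article.

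**The concern.** The sentence in section 3.3 fits a two-arm trial. It can be read in two ways here, and neither works. Read literally, it compares two groups, and there is only one. Read as initial against final, it treats 40 patients measured twice as 80 unrelated people.

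The second reading ignores the within-patient correlation. When that correlation is positive, as is to be expected for the same index in the same patients 3 months apart, the unpaired test overstates the standard error of the change. The intervals are then too wide, the P values tend to be too large, and a real change is easily missed. With only 40 patients and no control arm, the before-after comparison is all the inference the trial has, so a real effect could be reported as no effect.

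Two further points follow.

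- **Different patients at the two times.** An unpaired comparison allows the initial and final samples to differ. If patients with poor HRV leave and all available values are used, the final mean rises without any change in anyone.
- **Normality.** If the Shapiro–Wilk result decides which test is used, it should be applied to the within-patient differences and not to the raw values.

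**Working it through.** **Inputs from the article.** One group; n = 40 (sections 2.6 and 3.1); two HRV assessments per patient (2.6, 2.7); significance level 0.05 (3.3), taken here as two-sided.

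**Inputs the article does not give (assumed).** Within-patient correlation r from 0 to 0.7; equal SDs at both times; normal data; all 40 patients complete; true change 0.4 SD. The sample size of 40 comes without power, effect size or SD, so there is no planned figure to reproduce.

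**Standard error of the mean change, in SD units.**

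- Used by the unpaired test: √(2/n) = √(2/40) = 0.224, whatever r is.
- Correct for the same patients: √(2(1 − r)/n). At r = 0.5 this is √(1/40) = 0.158; at r = 0.7 it is √(0.6/40) = 0.122.
- Ratio: 1/√(1 − r), which is 1.41 at r = 0.5, 1.58 at 0.6 and 1.83 at 0.7. Confidence intervals are too wide by nearly the same factor.

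**Real type I error of the unpaired test.** Approximately 2 × [1 − Φ(1.96/√(1 − r))]. At r = 0.5: 1.96 × 1.414 = 2.77, giving 0.56%. Simulation with the actual *t* test gives 0.64%.

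**Simulation.** 500,000 trials per row, n = 40 pairs:

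| r | SE ratio | Type I error, unpaired | Type I error, paired | Power at 0.4 SD, unpaired | Power at 0.4 SD, paired |
|---|---|---|---|---|---|
| 0 | 1.00 | 5.0% | 5.0% | 42% | 41% |
| 0.2 | 1.12 | 2.9% | 5.0% | 41% | 50% |
| 0.3 | 1.20 | 2.0% | 4.9% | 41% | 55% |
| 0.5 | 1.41 | 0.64% | 5.0% | 39% | 69% |
| 0.6 | 1.58 | 0.26% | 5.0% | 38% | 79% |
| 0.7 | 1.83 | 0.06% | 5.0% | 37% | 89% |

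Unpaired power does not rise with r because the expected statistic is fixed at about 0.4/0.224 = 1.79, below the critical value of about 1.99. For a 0.5 SD change, a separate simulation of 40,000 trials gives unpaired against paired power of 62% v 74% at r = 0.3, 64% v 87% at 0.5 and 67% v 98% at 0.7.

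**Mann–Whitney.** It fails in the same way: its simulated type I error (4,000 trials) is 1.9% at r = 0.3, 0.65% at 0.5 and about 0.2% at 0.7.

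**Skewed data, as an illustration.** With lognormal values (assumed log-SD 0.8, r = 0.7, true ratio 1.3), the planned route of Shapiro–Wilk and then an unpaired test has 18% power. A paired route with Shapiro–Wilk on the differences has 67%, and a paired *t* test on logs has 74%.

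**Dropout, as an illustration.** If a share p leaves whose initial mean is g SD below that of the patients who stay, and all available values are used, the final mean exceeds the initial mean by p × g with no true change. With p = 20% and g = 0.5 to 1 SD, that is 0.2 × 0.5 = 0.10 to 0.2 × 1 = 0.20 SD.

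**The case against.** The mismatch between test and design cannot be explained away, but four objections limit what may be claimed from it.

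1. **The size depends on a correlation the article does not give.** At r = 0 the unpaired test is valid, and at r = 0.2 to 0.3 the power loss is about 9 to 14 percentage points, not 50. This stands, and the table shows the range. No correlation at all between repeated values in the same patients is implausible, and any positive value pushes the error in the same direction.
2. **The error is conservative.** With positive correlation the test gives fewer false positives, not more. This also stands: the cost is missed effects and intervals that are too wide. A negative correlation would reverse it (type I error about 7% at r = −0.2), but that is unlikely here.
3. **The dropout artefact is conditional.** Section 3.3 does not say that patients without a final value stay in the initial mean, and an unpaired test on completers only would not show it. The 20% and the 0.5 to 1 SD are assumptions. The figure shows what the wording permits and is not needed for the conclusion.
4. **The normality sentence follows the choice between mean and median for description, where raw values are the right ones to test.** That is fair for description. It does not carry over to the choice between a parametric and a nonparametric test of change.

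It might also be said that a fuller analysis plan would settle the matter. But the article does not leave the test open: it names one that contradicts its own design.

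**Conclusion.** The point holds and must be corrected before analysis. The only inferential tests stated are for two independent samples, and the trial has one sample measured twice. That conclusion rests on the text alone.

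Its size rests on assumptions: 40 complete pairs, equal SDs, a true change of 0.4 SD and a positive correlation. At correlations of 0.5 to 0.7 the planned *t* test has 37–39% power where a paired test has 69–89%, and its nominal 5% level is really between 0.06% and 0.64%. At 0.2 to 0.3 the power is about 41% against 50–55%. The main risk is a real change reported as none. A spurious gain from dropout is a secondary risk, and only if all available values are used. Section 3.3 states no other inferential method, so the error affects HRV and also quality of life wherever initial and final scores are compared.

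**What to change.** Replace the test sentence in section 3.3 with wording such as:

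> Within-patient change (final minus initial) will be analysed by the paired *t* test, with the mean change and 95% confidence interval, or by the Wilcoxon signed-rank test. Normality will be assessed on the within-patient differences.

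Delete the reference to a comparison between groups. Raw values may still be checked for normality to decide how to describe them.

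Two additions are worthwhile but not essential. HRV indices that prove right-skewed can be log-transformed and reported as a geometric mean ratio with 95% confidence interval. Patients with one missing visit can be kept in a mixed model with visit as a fixed effect and patient as a random effect. The paired test uses completers only; that removes the artefact of comparing different sets of patients but does not cure all attrition bias.

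The cost is one paragraph. No new data or patients are needed, and all these methods are available in SPSS, the package already named. Section 3.1 says recruitment is under way, so the change should be dated and made before the final data are analysed.

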## Discussion

4

The ANS dysfunction is commonly present in patients with CRD and in patients undergoing hemodialysis and it is an independent factor for a worse prognosis and sudden cardiac death in this population.^[7,8]^ Dysfunction of the ANS has been related to cardiovascular events in patients with CRD.^[7–9]^ Several studies have shown the relationship between HRV reduction and the development of complex arrhythmias in these patients.^[7–9]^ Generally, in the most advanced stage of this pathology, there are changes that are noticed in almost all systems of the body: nervous, cardiovascular, respiratory, musculoskeletal, immunologic, and endocrine/metabolic.^[7–9]^

Physical training in normal individuals leads to increased functional capacity, reduces the risk of cardiovascular diseases, and improves the psychologic structure. Similar benefits have been reported in dialysis patients,^[24]^ even though the actual impact is frequently impaired by the difficulty of adhering to any exercise program, both by sick individuals and by healthy individuals.

Physical activity promotes favorable physiologic adaptations, leading to an improvement in QoL. Following this reasoning, the implementation of an exercise program during hemodialysis sessions is a safe and efficient intervention that helps improve physical performance, nutritional status, QoL, anabolic response, and muscle strength.^[25,26]^

Exercise prescription for patients with CRD is less common than for other chronic diseases; this is notable considering that the levels of physical activity of patients with CRD are significantly lower than among healthy individuals.^[15]^ Despite this, there are indications that exercise can improve physical functioning and positively impact mediators of diseases, comorbidities, and factors associated with the progression of renal disease.^[27]^

Research that can investigate better ways to achieve positive results, with the intention of producing new knowledge and becoming products that will improve the health of the population is important. This could be a new diagnosis, new therapeutic treatments, or actions aimed at promoting the health of the population.^[28,29]^ Corroborating with the authors, the study intends to propose a quality protocol that is both safe and reliable in its execution and data generation, providing reliable information for the health arena. This protocol is expected to be a better indicator of the improvement of the health of patients with CRD who are undergoing hemodialysis treatment.
